### Safety assessments

In our multidomain intervention strategy, the exercises are submaximal, and the primary form of nutritional intervention is dietary guidance. Therefore, the multidomain intervention in this study is considered safe, and no adverse events are expected during the intervention period. Nonetheless, any adverse events will be documented and reported to the principal investigators and the ethics committee within 24 h.

## Discussion

In the field of geriatrics, the exploration of interventions to delay aging is an emerging topic that promotes healthy aging. From an economic perspective, extending healthy life expectancy by 2.2 years could save $7 trillion in social healthcare expenditures over 50 years [58]. Exploring interventions to delay aging is considered a more meaningful medical investment than researching disease treatments. It not only helps extend the healthy lifespan of older adults but also brings significant benefits to public health and healthcare systems [3]. Therefore, we believe that multidomain intervention can be applied in the field of aging. It aligns with the goal of healthy aging, has the potential to maintain physical function and combat aging, and serves as proactive health-promoting measures for older populations.

This study strictly references the research designs of completed or ongoing multidomain intervention studies internationally. For example, FINGER [59] aims to investigate the efficacy of multidomain intervention in preventing cognitive impairment, involving populations from six regions in Finland. The two-year intervention duration covers dietary adjustments, physical exercise, cognitive training, and cardiovascular risk management. Xu et.al [33] implemented the SINGER (SINgapore GERiatric Intervention Study to Reduce Cognitive Decline and Physical Frailty) study aimed at slowing cognitive decline and frailty. In Malaysia, the WE-RISE study [32] and the AGELESS study [60] have been conducted to reverse cognitive decline. Chen LK et.al [14] also carried out the THISCE study to improve physical frailty and cognitive function among community-dwelling older adults.

We drew inspiration from the above-mentioned studies in our intervention model, combining group interventions with individual family-based interventions. The group intervention involves a physician-led 2-hour session where older adults will participate in cognitive training 60 min, exercise training 45 min, and nutritional intervention 15 min. The duration of the group intervention is designed considering the limited energy and attention span of older adults. The group intervention will be held biweekly for a total of 10 sessions, differing from the gradual reduction in intervention frequency seen in other studies. For example, the THISCE study spanned 12 months with weekly sessions in the first month, biweekly sessions in the second month, and monthly sessions for the remaining 10 months [14]. Given that our study is a short-term intervention lasting 6 months, to ensure participants’ training volume and compliance, we consider that a biweekly group intervention frequency may be suitable in practice.

Currently, some scholars have conducted intervention studies targeting biological age. Most of these studies have implemented dietary and exercise interventions in obese populations. For example, a one-year intervention combining diet and exercise in 107 obese older adults found that both the diet group and the diet-plus-exercise group showed a reduction in Klemera Doubal Method (KDM) biological age at the 6-month and 12-month follow-up assessments. Specifically, at 6 months, the diet group showed a reduction of 1.4 years, while the diet-plus-exercise group showed a reduction of 1.7 years. At 12 months, the diet group showed a reduction of 2.4 years, and the diet-plus-exercise group showed a reduction of 2.2 years [61]. In the Israeli CENTRAL study, 120 obese individuals underwent an 18-month weight-loss intervention combining diet and exercise, which resulted in a 7.1-month delay in methylation age compared to the expected aging in the older male subgroup [62]. Similarly, a U.S. study involving 16 obese older adults implemented a 3-month intervention consisting of dietary counseling and a combination of aerobic and resistance exercise. However, this study found no statistically significant reduction in three types of methylation age (Horvath, Hannum, and PhenoAge clocks) after the intervention [63]. In the widely recognized CALERIE study on caloric restriction, 128 normal-weight or mildly overweight participants underwent a 25% caloric restriction for 2 years. The pace of aging, as measured by DunedinPACE, slowed by 2%∼3% in the caloric restriction group (equivalent to a 10%∼15% reduction in mortality risk), but no significant changes were detected using the other two aging clocks (PC-PhenoAge and PC-GrimAge) [64].

Additionally, some studies have explored aging interventions in relatively healthy populations. The European NU-AGE study [65] enrolled 120 older adults aged ≥65 years (60 Italians and 60 Poles) to assess the effects of a 1-year Mediterranean diet intervention on methylation age. The results showed that only the Polish female subgroup experienced a reduction in Horvath methylation age acceleration by 1.47 years, suggesting that the Mediterranean diet may promote epigenetic rejuvenation, although this effect varied by country, gender, and individual specificity. Fitzgerald et al. [66] first conducted a 2-month multi-domain intervention involving diet, exercise, sleep, and relaxation guidance in 43 healthy adult males aged 50–72 years, which resulted in a reduction of Horvath methylation age by 3.23 years. Subsequently, they tested the same intervention in 6 females aged 46–65 years, and the participants’ methylation age decreased by an average of 4.6 years after the intervention [67].

Looking at the above intervention studies using methylation age or KDM biological age as outcome measures, most studies were not originally designed with aging as the primary focus, leading to some bias in the study populations. Additionally, variations in sample size, ethnicity, gender, and specific outcome measures limit the generalizability of these findings. Nevertheless, the diverse intervention strategies explored in these studies offer valuable insights for researchers. While the majority of prior studies have focused on combined diet and exercise interventions, the multidomain intervention in this study integrates cognitive training, exercise training, and nutritional guidance. To date, limited literature has applied a similar intervention protocol to methylation age. Our study may provide new evidence for clinical interventions targeting aging. Furthermore, the aforementioned studies on the reversal effects of methylation age involved intervention durations ranging from 2 months to 2 years. Considering that our intervention encompasses a broader range of components, we have established a moderate intervention duration of 6 months. We hypothesize that this multi-domain intervention may have a decelerating effect on aging.

In the design of individual family-based intervention programs, we have integrated the use of traditional paper materials and mobile medical platforms. Participants can refer not only to paper exercise charts but also follow exercise training videos when exercising at home. The mobile medical platform can assist healthcare providers in monitoring and supervising the participants’ home training progress, while also providing opportunities for communication and feedback between participants and healthcare providers, thus facilitating the entire intervention process. The older population is likely to encounter some challenges in learning to use the mobile medical platform, but this also presents an opportunity for them to enhance their daily living and cognitive abilities, as well as integrate into society. In our group interventions, we will provide operational training on platform usage for older participants and encourage their family members to also participate in guiding home interventions. The combined form of group interventions with individual family-based interventions aims to enable participants to apply what they learn in group interventions to their daily lives, gradually cultivating healthy lifestyle habits. Our intervention approach emphasizes that participants should not solely rely on healthcare providers for completing the intervention but rather prioritize their own proactive engagement in training at home. This approach aligns with the concept of active health promotion among older adults.

Our study may provide compelling evidence that practical and sustainable multidomain intervention measures could be implemented using simple materials and facilities. The auxiliary equipment used in exercise training such as resistance bands, dumbbells, and sandbags are readily available and can be used at home, even with all exercises achievable using just a resistance band. Materials for cognitive training and nutritional guidance include booklets, visual aids, or cards, all of which are low-cost and reusable. While the primary goal of this study is not to assess the cost-effectiveness of multidomain intervention, our design considers economic feasibility, with intervention costs being relatively affordable, independent of specialized medical environments or equipment, thus saving healthcare resources.

In this study, we chose epigenetic clocks as the primary outcome measures due to its well-established role as a biomarker of biological aging and its sensitivity to lifestyle interventions. Geriatricians can utilize the DNA methylation age to explore the underlying mechanisms of aging, investigate factors related to aging, and evaluate the effectiveness of aging interventions [68]. In addition, there are dedicated online platforms and open-source R packages for calculating the methylation age. This enables the use of methylation age as a biomarker for quantifying aging in different populations, and also makes the results of various studies comparable and generalizable. If this study is successfully implemented, it will provide valuable experiences and models for health management and aging intervention for older populations in other regions. With the context of an aging society, our findings may provide new insights for public health managers in promoting proactive health, which involves leveraging existing healthcare resources and community networks to enhance the health and well-being of older adults.

There are also inherent limitations to the study design. Participants and the intervention staff could not be blinded due to the nature of our intervention contents. We do not consider this to be a significant issue as we will employ blinding for outcome assessors and utilize a Zelen-design for randomized controlled trial which is more in line with clinical practice reality. Additionally, we plan to conduct one-to-many teaching operations in the group intervention rather than one-to-one due to manpower costs. While this may impact the intervention’s effectiveness, it is a common issue when generalizing intervention models to more community healthcare institutions with more participants. We need to explore the most cost-effective intervention strategy in future practice. Moreover, our study will exclude participants with moderate to severe cognitive dysfunction (MMSE score *≤* 20) to ensure ethical rigor and protocol compliance. Although this approach enhances the internal validity of our findings, it may limit the generalizability of the IC results to populations with cognitive impairment. Future studies should explore IC in individuals with cognitive dysfunction to provide a more comprehensive understanding of this construct.

Another limitation of the current study is that we evaluated the combined effect of cognitive training, exercise, and nutrition interventions without isolating the individual contributions of each component. This approach was adopted due to practical considerations, including sample size limitations and the complexity of the study design. In future studies, we plan to first conduct a single-center pilot intervention study, followed by a multi-center study with a larger sample size. In the multi-center study, participants will be randomized to different intervention groups (e.g. cognitive training alone, exercise alone, nutrition alone, and their combinations) and followed up for a longer period of time. This design will allow for a more precise evaluation of the independent and interactive effects of each intervention component.

Although the SilverHealth Pro Platform employed in this study presents several advantages, like real-time data collection and personalized feedback, it may pose usability challenges for older adults. Potential barriers include limited familiarity with technology and psychological resistance to new tools. To address these challenges, we are implementing some improvement strategies, such as simplifying the user interface, incorporating voice-assisted features, providing hands-on training, and offering ongoing technical support. In the future, we plan to recruit a small group of older adults to test the SilverHealth Pro Platform. Based on the participants’ feedback, we will optimize the platform’s design to enhance its usability and improve user compliance. In addition, we will provide alternative solutions (such as paper-based records or telephone follow-ups) for older individuals who indeed have difficulty using the mobile health platform.

To the best of our knowledge, there is currently no literature reporting on the multidomain intervention involving cognition, exercise and nutrition for delaying aging. Therefore, the present study aims to introduce a new approach to delaying aging and offer a practical multidomain intervention strategy for healthcare institutions.

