### Participants and recruitment

The trial will be conducted at the Fujian Provincial Center for Geriatrics. Recruitment will be conducted through printed posters in outpatient departments of Fujian Provincial Hospital and community health service centers, as well as electronic poster dissemination *via* WeChat groups and social media accounts. Interested participants will register by contacting the recruitment staff. Physicians from the Fujian Provincial Center for Geriatrics will carry out the screening according to the inclusion and exclusion criteria.

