### Inclusion and exclusion criteria

Inclusion criteria: (1) aged between 60 and 85 years old; (2) living in the community; (3) a smartphone user.

Exclusion criteria: (1) severe neurological disorders (e.g. Alzheimer’s disease, vascular dementia, Parkinson’s disease, history of stroke with significant residual disability), severe psychiatric disorders (e.g. active major depressive disorder, schizophrenia or bipolar disorder), or moderate to severe cognitive dysfunction (MiniMental State Examination score ≤ 20); (2) conditions causing significant motor function impairment (e.g. severe arthritis, spinal cord injury, or muscular dystrophy), or recent fractures or surgeries within the past 6 months that limit mobility; (3) severe speech, language, hearing, or visual impairments that hinder communication with study personnel or participation in the intervention; (4) inability to perform basic activities of daily living independently, as defined by a Barthel Index score ≤ 40 or a Katz Index score ≤ 2; (5) terminal malignant diseases with a life expectancy of less than 6 months; (6) inability or unwillingness to provide informed consent or agree to follow-up.

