### Randomization, blinding, and allocation concealment

Participants who meet the inclusion and exclusion criteria will be randomized into intervention and control groups in a 1:1 ratio. The randomization process will be carried out by a data custodian not involved in the study. The data custodian will generate a set of random numbers using a simple randomization procedure and place into sequentially numbered, sealed, opaque envelopes. The random numbers will be assigned to participants in numerical order. Participants in the intervention group will be informed about the intervention procedure and follow-up plan, while participants in the control group will be informed about the follow-up plan. If participants agree to their assigned plan, they will sign the informed consent and undergo further baseline assessment.

Due to the difficulty of blinding intervention implementers and participants in a multidomain intervention, data collection personnel and statistical analysts will be blinded to reduce bias. Participants are instructed not to disclose their group assignment to anyone during baseline and follow-up assessments.

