**Figure 1. F0001:**
[figure not shown]
Example of mobile check-in records through the ‘SilverHealth Pro Platform’ app in the individual family intervention. a: The main interface of the app allows participants to begin documenting their exercise training, cognitive training, and dietary records by clicking on ‘MIDA Health Diary’ Participants can view exercise examples in the form of pictures or videos by selecting different exercise options. b: In the exercise training section, participants will log the number of completed groups for each exercise movement. c: In the cognitive training section, participants will record the number of pages completed or the duration spent on each cognitive task from the cognitive training workbook. If needed, they can also upload pictures of the completed tasks. d: In the dietary record section, participants will sequentially log their daily meals, including staple foods, protein-rich foods, vegetables, fruits, and fats. If needed, they can upload pictures of their meals and add notes about the number of diners. This figure originates from software owned by the Fujian Provincial Center for Geriatrics and Fujian Provincial Institute of Clinical Geriatrics.

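### Individual simple randomisation with no household rule, combined with encouraged family involvement at home, would split about half of any enrolled couples and expose the control spouse to home content

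*Protocol article*

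**What the plan says.** All statements are in the protocol article.

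- **Allocation** (Randomization, blinding, and allocation concealment): the rule reads "Participants who meet the inclusion and exclusion criteria will be randomized into intervention and control groups in a 1:1 ratio". Its method is stated: "The data custodian will generate a set of random numbers using a simple randomization procedure". So is the order: "The random numbers will be assigned to participants in numerical order". The unit is the person, and no household element appears.
- **Eligibility** (Inclusion and exclusion criteria): the inclusion list is "1) aged between 60 and 85 years old; (2) living in the community; (3) a smartphone user". Neither list limits enrolment to one person per household.
- **Recruitment** (Participants and recruitment): posters, WeChat groups and social media, then self-registration: "Interested participants will register by contacting the recruitment staff".
- **Home component** (Intervention group; Discussion): exercise, cognitive training and dietary records three times a week, supported by a take-home booklet, exercise charts and videos. Staff will also "encourage their family members to also participate in guiding home interventions". The Figure 1 legend lets participants, where needed, "add notes about the number of diners" in the meal log.
- **Control condition** (Control group): six monthly lectures.
- **Non-disclosure** (Randomization section): participants are told not to reveal their arm at assessments. Nothing covers sharing content at home.

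The limitations in the Discussion mention neither households nor contamination.

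**The concern.** Individual allocation and family support for home training are each reasonable alone. Together they weaken the contrast under test. When two spouses both enrol and are split, the obvious family helper for the intervention participant is a member of the control arm.

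Two consequences follow. First, a control participant who shares the exercises, cognitive tasks or altered meals may shift in the same direction as the intervention arm. That shrinks the between-arm difference in the epigenetic clocks, frailty and intrinsic capacity, and makes a null result harder to interpret.

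Second, controls are told only the follow-up plan, and consent follows allocation. A control spouse may learn what the other arm receives, possibly before signing. Baseline assessment comes after consent, and the analysis set requires baseline plus one follow-up. A refusal prompted by that knowledge would therefore remove the person from the analysis, and only from one arm.

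**Working it through.** **1. Reproduce the plan's figure.** Inputs from Calculation of sample size: 74 per group for 90% power, 20% dropout, 75% adherence.

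74 / (0.80 × 0.75) = 123.3, rounded up to 124 per group, 248 in total. This matches. The inflation covers dropout and non-adherence; no allowance for control-arm contamination is stated. The 74 itself cannot be re-derived, because no standard deviation is given, so the stated 90% is taken as the starting point.

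**2. Chance that a couple is split.** Two independent 1:1 allocations differ with probability 0.50 (124/247 = 0.502 if the arms were fixed at 124). The probability of at least one split among k couples is 1 − 0.5^k: 0.97 for k = 5 and 0.999 for k = 10.

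**3. Dilution.** Let c be the share of participants enrolled as couples and s the share of the effect that passes to a control spouse. The documents give neither; both are assumptions. The share of controls with a spouse in the other arm is c/2, so the effect is multiplied by 1 − d, with d = (c/2) × s.

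As a guide to scale, c = 10% of 248 is about 25 people or 12 couples. About 6 would be split, giving about 6 exposed controls out of 124 (5%).

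**4. Power.** With two-sided α = 0.05 (Statistical analysis), 90% power corresponds to 1.96 + 1.28 = 3.24 standard errors. Diluted power = Φ(3.24 × (1 − d) − 1.96). The evaluable number needed to restore 90% is 74 / (1 − d)², rounded up. Dividing by 0.60 and rounding up gives the recruits per arm.

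| c | s | d | Power | Recruits per arm for 90% |
|---|---|---|---|---|
| 10% | 25% | 0.0125 | 89.3% | 127 |
| 10% | 50% | 0.025 | 88.5% | 130 |
| 10% | 100% | 0.05 | 86.9% | 137 |
| 20% | 25% | 0.025 | 88.5% | 130 |
| 20% | 50% | 0.05 | 86.9% | 137 |
| 20% | 100% | 0.10 | 83.1% | 154 |
| 40% | 25% | 0.05 | 86.9% | 137 |
| 40% | 50% | 0.10 | 83.1% | 154 |
| 40% | 100% | 0.20 | 73.7% | 194 |

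Worked row: c = 20%, s = 100% gives d = 0.10; 3.24 × 0.90 − 1.96 = 0.96; Φ(0.96) ≈ 0.83.

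The comparison is with 124 planned. These figures ignore correlation between spouses' outcomes.

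**The case against.** The strongest reply is that this argues from silence in a condensed article. Nothing says couples will enrol, no stated figure is wrong, and a fuller protocol might hold a household rule. That last possibility stands, and such a rule would close the point. But the article sets out its eligibility lists and envelope procedure in detail, and the problem comes from two things it does state: individual allocation and encouraged family involvement.

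Three stronger readings are tempting, and the documents support none of them.

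- **That the control spouse receives the intervention.** The family sentence sits beside text on learning to use the app and speaks of guiding the participant. The group sessions, staff-adjusted tasks and individual dietary feedback do not reach the spouse. The note on diners is optional and shows only that meals may be shared. Controls also hear lectures on exercise and diet by design.
- **That the benefit of the Zelen design is lost.** Study design gives several reasons for it, including compliance and fit with practice. The benefit is weakened only for members of split couples.
- **That contamination would leave no trace.** Physical activity, sedentary time and dietary diversity are measured in both arms at every visit (Table 1), so behaviour change among controls would show. What is missing is the link: marital status is collected (Questionnaires), but no listed item records a partner's enrolment.

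The full spill-over rows are also severe. They give the control spouse the whole effect without group sessions or feedback, while the plan itself assumes 75% adherence.

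**Conclusion.** The point holds as a design gap whose size is uncertain. Following the text as written splits about half of any enrolled couples, exposes those control spouses to home content, and biases the comparison towards no difference, provided that the exposure acts in the same direction as the intervention. Across the assumed ranges, power falls from 90% to between about 89% and 74%. The 74% needs two-fifths of participants in couples and complete spill-over, so it is a bound and not an expectation. With few couples or modest spill-over the loss is one or two percentage points. The 124 per group is not an arithmetical error. The reason to act is that prevention is cheap and a split couple cannot be undone after allocation.

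**What to change.** Add one screening question: is another member of the household registering? Then adopt one of two rules in the eligibility and randomisation sections.

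- **Allocate by household.** Give all eligible members one envelope, opened only after all of them have registered. Keep a household identifier. The repeated-measures analyses in Statistical analysis have no household term, so add a household random effect or cluster-robust standard errors. A mixed model would also agree with the one named in Calculation of sample size. Cost: possible small arm imbalance and slight within-pair correlation. The variance rises by a factor of about 1 + cρ, where ρ is the within-couple correlation, which the documents do not give.
- **Enrol one person per household.** The analysis stays as planned. Cost: a few volunteers lost.

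Either rule removes the dilution from split couples. Apart from the screening answer and, under the first rule, the identifier, no further data are needed.
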